**Methods:**

This evaluation study is a cluster randomized controlled trial, in which the study centers will be randomly assigned either to the intervention group or the control group. Study centers will recruit relatives of and patients with DM type 1 and type 2. Members of the intervention group will participate in the education program Dia*Life*, whereas participants randomized in the control group will act as waiting-list controls. The study will assess the efficacy of Dia*Life* by comparing diabetes-related knowledge between the intervention and control groups as the primary outcome for participants. As the primary outcome in patients, the Hba1c value will be assessed. In addition, diabetes-related distress, family interaction, and other secondary endpoints will be considered as secondary outcomes. Long-term efficacy will be assessed 6 and 12 months after intervention. Hierarchical regression models will be used to analyze effects over time.

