#### Quantitative assessment

All relatives and patients will be asked to complete questionnaires at four different times, with baseline assessment at recruitment. Participants assigned to the intervention group will fill out a second questionnaire (follow-up 1) after completing the implemented intervention. Participants in the control group will also fill out a second questionnaire after an interval of approximately 8 weeks. In both groups, the second and third follow-ups will take place 6 and 12 months after follow-up 1, respectively. Parallel to all four moments of assessment, participating CDEs will be asked to complete a questionnaire for each patient in order to ascertain patients’ current health condition, their latest recorded Hba1c value, and their current diabetes treatment. Participants will be invited to all four assessments by postal reminder.

The data input will be performed successively. As soon as missing data are noticed, the study team will contact the corresponding CDE. The CDE will be asked to contact and remind the participants to provide missing data. The CDEs are also asked to report any drop-out as soon as it occurs.

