### Primary outcomes

#### Participating relatives

Difference in knowledge about diabetes between relatives of the intervention and control groups was determined as the study’s primary endpoint. Participants will be asked to answer knowledge-based questions before and after intervention (intervention group) or during regular consultation and care (control group). Result examination focuses on the question regarding if and to what extent knowledge has increased after the implemented intervention. Therefore, two questionnaires assessing relatives’ knowledge about diabetes type 1 or type 2 will be applied. These questionnaires will be developed following the templates used by Kronsbein et al. [18], that have already been applied by Pieber et al. [12]. Both questionnaires will consist of 16 questions regarding, for example, the impact of insulin on blood glucose, symptoms, causes and treatment of hypoglycemia and hyperglycemia, diabetes-related comorbidities, blood glucose monitoring, and impact of certain foods on the blood glucose level. In addition, the questionnaire for relatives of patients suffering from diabetes type 1 includes questions about glucagon shots, symptoms and treatment of ketoacidosis, and carbohydrate units. Relatives of patients with diabetes type 2 are additionally asked about the impact of certain factors (e.g. eating behavior) on blood glucose and what kind of preventive medical checkups are generally advised. The questionnaires used are available upon request from the authors. A translated version of the questionnaire is available in Additional files 2 and 3.

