### Data analysis

#### Primary endpoint

A linear model with intervention as a fixed factor and study center as a random factor will be conducted. The estimated main difference between the intervention and control groups for a confidence level of 95% at a 5% significance level will be reported. Moreover, subanalyses of type 1 and type 2 participants are planned to assess Dia*Life*’s efficacy among relatives and patients with diabetes mellitus type 1 and type 2 independently.

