#### Secondary endpoint

Metric: a linear metric model with intervention as a fixed factor and study center as a random factor will be conducted.Binary: a linear mixed model with intervention as a fixed factor and study center as a random factor will be conducted.

The significance level is α = 0.05. To counteract the effect of multiple testing, an adequate correction will be conducted.

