### Limitations

The evaluation study might be limited by using a cluster randomization of study centers instead of an individual randomization of participants. However, after careful consideration, the study team decided on a cluster randomized trial because of the practical implementation.

Relatives of patients with diabetes who have already participated in another education program for diabetes will not be excluded. Varying levels of diabetes-related knowledge and skills might affect Dia*Life*’s evaluation. However, since participating relatives’ state of knowledge will be evaluated in the baseline assessment, it is possible to control for this confounding variable in the analysis.

In addition, the Dia*Life* education program is designed for the healthcare situation in Germany and benefits from existing structures of diabetes care. However, these structures might be different in other countries. Thus, the Dia*Life* program might not be applicable elsewhere. Moreover, the curriculum of the Dia*Life* education program so far exists in German only, which might restrain non-native speakers from participation.

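### The stated models contain no visit or baseline term and name no assessment, so they do not deliver the analysis over time that the abstract announces

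*Protocol article*

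**What the plan says.** The abstract (Methods) makes two commitments: "Long-term efficacy will be assessed 6 and 12 months after intervention" and "Hierarchical regression models will be used to analyze effects over time".

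The section Quantitative assessment fixes the data: "All relatives and patients will be asked to complete questionnaires at four different times, with baseline assessment at recruitment". It then adds: "In both groups, the second and third follow-ups will take place 6 and 12 months after follow-up 1, respectively".

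The section Data analysis, Primary endpoint, gives the model: "A linear model with intervention as a fixed factor and study center as a random factor will be conducted". It goes on to report one estimated difference between the groups with a 95% confidence level. Under Secondary endpoint, metric outcomes get "a linear metric model with intervention as a fixed factor and study center as a random factor will be conducted", and binary outcomes get the same two terms.

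Two other places bear on the reading. Primary outcomes, Participating relatives, says: "Result examination focuses on the question regarding if and to what extent knowledge has increased after the implemented intervention". The Limitations section says of prior knowledge, measured at baseline, that "it is possible to control for this confounding variable in the analysis".

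**The concern.** The abstract and the analysis section describe different analyses. Modelling an effect over time needs a term for visit and one for intervention by visit. The analysis section has neither. It also does not say which of the four assessments supplies the outcome, or that the model is repeated at each one. Baseline knowledge is described as controllable, yet no model sentence contains it.

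Several analyses therefore fit the published wording: follow-up 1 alone, each follow-up separately, or some pooling of visits. They need not agree. The Background says that a positive evaluation is required for certification, so the visit that carries the primary test should be fixed in advance. The 6- and 12-month results should also have a stated analysis.

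**Working it through.** **1. The plan's own figure.** From Power calculation and sample size: 12 per group before corrections, 10% drop-out, 11 relatives per center, ICC 0.21.
- Drop-out: 12 / 0.9 = 13.3, rounded up to 14.
- Design effect: 1 + (11 − 1) × 0.21 = 3.1.
- 14 × 3.1 = 43.4, rounded up to 44; 44 × 4 cells = 176 relatives.

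This reproduces the plan. The calculation has no term for repeated visits, so naming one primary visit leaves it unchanged. The starting 12 cannot be checked because no SD is given. With n = 2 × (1.96 + 1.2816)² × SD² / 29², n = 12 corresponds to an SD of about 21.9 points (about 20.9 with a t-test). I use 21.9 below as an assumption.

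**2. Terms announced against terms stated.**

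| Term | Announced or implied | In the stated models |
|---|---|---|
| Intervention | yes | yes, fixed |
| Study center | yes | yes, random |
| Visit, intervention by visit | yes (Abstract) | no |
| Baseline value | called possible (Limitations) | no |
| Assessment used | follow-up 1 implied (Primary outcomes) | not named |

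**3. What the stated model gives, depending on how it is applied.** Assumptions: one diabetes type, 4 centers of 11 per arm, SD 21.9, ICC 0.21 constant over time, 29 points at follow-up 1, two-sided 5%. Power is by normal approximation unless noted.

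*Follow-up 1 only.* Variance of the arm difference = 2 × SD² × (ICC + (1 − ICC)/11) / 4 = 2 × 479.6 × (0.21 + 0.0718) / 4 = 67.6, so SE = 8.22. 29 / 8.22 = 3.53, which gives power of about 94% (about 83% with a t-test on 6 df for 8 centers). There is no dilution.

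*Each follow-up separately.* I simulated 4,000 balanced trials with true effects of 0, 29, 20 and 10 points at the four assessments and a within-person correlation of 0.5 inside centers. The per-visit arm differences averaged −0.2, 28.7, 19.8 and 9.8, so they recover the true values. Pooling all four assessments gave 14.5 (true mean 14.75).

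*Visits pooled without a visit term.* With k visits, (1 − ICC)/11 becomes (1 − ICC) × [(1 + (k − 1)ρ)/k] / 11, where ρ is an assumed within-person correlation of 0.3 to 0.9.

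| Pooled assessments | Effect at 6 and 12 months | Average effect | Power |
|---|---|---|---|
| All four | sustained at 29 | (0 + 29 + 29 + 29)/4 = 21.75 | 76–81% |
| All four | halved | (0 + 29 + 14.5 + 14.5)/4 = 14.5 | 43–47% |
| All four | lost | (0 + 29 + 0 + 0)/4 = 7.25 | 14–16% |
| Three follow-ups | halved | (29 + 14.5 + 14.5)/3 = 19.3 | 66–71% |
| Three follow-ups | sustained at 29 | 29 | no dilution |

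The article describes none of these pooled analyses. The table shows only why the visit should be named.

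**4. Change over time.** In the simulated example the effect falls by 29 − 10 = 19 points between follow-up 1 and 12 months. Separate fits give 28.7 − 9.8 = 18.9, but no standard error for it: both estimates come from the same people, and separate fits carry no covariance between them. A pooled fit without visit has no such parameter at all. On either application, the change in effect is not tested.

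**5. Baseline.** A model without the baseline value is unbiased under randomization with complete data, but less precise than one that includes it. I do not put a figure on the loss, because the article gives no correlation between baseline and follow-up scores.

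**The case against.** The strongest reply is that this is a condensed article. Visit structure and covariates are commonly left to the full protocol or analysis plan, and the abstract shows that a longitudinal analysis is intended. Silence alone would indeed be no finding. Here, however, the article does state a model, and that model does not perform the analysis announced in the abstract. A fuller document may hold the right model, but the two published statements would still disagree.

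The word hierarchical is not contradicted, since a random study center makes the model hierarchical. Only the part about time has no counterpart.

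A reader might infer three stronger points, which the document does not support:
- *The primary estimate is biased toward zero.* This needs baseline scores averaged into the outcome. No section says so. The primary outcome is framed as knowledge gained after the intervention, which points to follow-up 1, and Limitations treats baseline as something to adjust for.
- *No 6- or 12-month result is possible.* The same model fitted at each follow-up gives those differences without dilution. Only the change between visits stays untested.
- *Standard errors are wrong because there is no participant effect.* That concerns arm-by-time contrasts, which the stated model does not contain. In a per-visit fit each person supplies one value, so no participant effect is needed.

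It is also fair to say that a per-visit analysis would be acceptable and that one joint model is not the only remedy.

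**Conclusion.** The mismatch is real and should be resolved before the analysis. The abstract announces effects over time and efficacy at 6 and 12 months. The stated models have only intervention and center, name no assessment, and leave out the baseline value. They cannot estimate or test change in the effect.

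The consequence is moderate. On the ordinary per-visit reading, the loss is some precision and the test of change over time, not validity. The figures of 21.75 points and below describe a pooling that the article does not propose. They also depend on an assumed course of the effect. The power figures further assume an SD of 21.9, the within-person correlations shown and a stable ICC. The planned 44 per cell is unaffected.

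**What to change.** Name the intervention contrast at follow-up 1 as the primary comparison. Replace the stated model with one mixed model of the follow-up values:
- fixed effects: intervention, visit (follow-ups 1, 2 and 3), intervention by visit, baseline value and diabetes type;
- random intercepts: center, and participant within center.

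Report the 6- and 12-month contrasts from that model as long-term efficacy, and use the interaction for change over time. Diabetes type belongs in the model because randomization is stratified by it and the knowledge questionnaire differs by type. The same structure serves HbA1c and the metric secondary endpoints.

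At minimum, state that the existing model, with the baseline value added, is fitted at each follow-up, and reword the abstract so that it no longer promises a model of effects over time.

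The cost is a change of wording and slightly more modelling work. All four assessments and diabetes type are already collected under the plan, so no new data are needed and the sample size does not change.

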#### Secondary endpoint

Metric: a linear metric model with intervention as a fixed factor and study center as a random factor will be conducted.Binary: a linear mixed model with intervention as a fixed factor and study center as a random factor will be conducted.

The significance level is α = 0.05. To counteract the effect of multiple testing, an adequate correction will be conducted.

#### Handling of missing data

Missing values will be handled with caution since they will not be avoidable. In the statistical analysis, appropriate techniques will be applied to handle missing data [25].

### Ethical considerations

The Ethical Review Committee of the University of Jena has approved this study in the first place. Since the study is designed to be multicentric and will therefore be executed by diverse German study centers, ethical approval from each federal state in which the study centers are located is required. Consequently, ethic approvals from Ethical Review Committees of the following State Chambers of Physicians were obtained: Saxony, Schleswig-Holstein, Baden-Wuerttemberg, Hesse, Saarland, Brandenburg, North Rhine, Westphalia-Lippe, and Rhineland-Palatinate. In Bavaria and Berlin, no ethic approvals are required given that the study has already been approved by the Ethical Review Committee of the University of Jena. The study will be performed in accordance with the Guidelines for Good Clinical Practice (ICH-GCP), the Declaration of Helsinki in its latest version, and international and local laws.

Participants will give their written consent. Only persons who provided valid informed consent will be included. Participants will obtain contact information for the study team in case of further information needs. The intervention in the form of the recently developed Dia*Life* education program is non-invasive and does not pose any risk to participants. Thus, no adverse events will be expected. Furthermore, to ensure participants anonymity, assessed data will be blinded of any identifying participant information and will be coded with an ID number. Only primary investigators and the data analyst will have access to the final dataset. The data collected will be held confidentially by the lead investigator and will be saved for 10 years. Protocol modifications will be recorded and disclosed to all relevant parties.

## Discussion

Education programs are the foundation of successful diabetes treatment and care, and also part of the guidelines for psychosocial aspects of diabetes [3]. Since diabetes disease not only affects patients themselves, but also their close relatives in certain areas of life, an education program is a promising way to create long-lasting positive effects for both patients and family members. Although several education programs for diabetes patients were certificated by the German federal insurance office, no certificated education program for patients’ relatives exists. So far, it was up to the CDE to invite relatives to patients’ education programs. However, the implemented focus group interviews, conducted in the first phase of the Dia*Life* project, revealed complications regarding a joint education course. Complications might occur when someone feels impeded by the presence of a close relative to express his/her feelings and opinions freely. Diabetes management and the involvement of relatives are therefore important fields of improvement. The Dia*Life* education program is the first German program designed for relatives of diabetes patients and attempts to increase primary relatives’ knowledge about the disease, as adequate and knowledge-based support can result in positive consequences for patients’ therapy compliance. Dia*Life* aims at strengthening relatives’ communication skills and empathy in order to interact in a supportive way with the patient. Dia*Life* also offers the benefit to exchange experiences with others who are affected, address their concerns to experts, and learn to accept feasible limitations imposed by the chronic disease. Since CDEs are already experienced in using education programs for patients, it can be assumed that the use of Dia*Life* can be implemented without complications in everyday practice. However, CDEs will be trained in the structure and content of Dia*Life* to ensure correct application. Implementing Dia*Life* as an education program for relatives of diabetes patients could also increase the general awareness that diabetes not only affects patients’ daily life, but also the life of their close relatives. It is aimed to report and publish the study’s results in peer-reviewed journals.

### Strengths

As this study uses a cRCT design, it can provide information on how the implementation of the Dia*Life* education program may contribute to improved diabetes management as perceived by relatives and patients. Based on the aim to reduce the probability of an imbalance between the intervention and control groups, block randomization was used [17]. Computer-based randomization lists were compiled using nQuery 7.0 at the ratio 1:1. To the best of our knowledge, this will be the first study to implement an education program for relatives in order to improve care of diabetes patients’ in Germany.

### Limitations

The evaluation study might be limited by using a cluster randomization of study centers instead of an individual randomization of participants. However, after careful consideration, the study team decided on a cluster randomized trial because of the practical implementation.

Relatives of patients with diabetes who have already participated in another education program for diabetes will not be excluded. Varying levels of diabetes-related knowledge and skills might affect Dia*Life*’s evaluation. However, since participating relatives’ state of knowledge will be evaluated in the baseline assessment, it is possible to control for this confounding variable in the analysis.

In addition, the Dia*Life* education program is designed for the healthcare situation in Germany and benefits from existing structures of diabetes care. However, these structures might be different in other countries. Thus, the Dia*Life* program might not be applicable elsewhere. Moreover, the curriculum of the Dia*Life* education program so far exists in German only, which might restrain non-native speakers from participation.

## Trial status

The recruitment of study centers started in March 2018 and was completed in December 2018. The recruitment of participating relatives and patients with diabetes mellitus started in August 2018 and was completed in June 2019.

Protocol Version 1.0 (July 25, 2019).

## Data Availability

Data sharing is not applicable to this article as no datasets were generated or analyzed during the current study.

## Abbreviations

CDE: Certified diabetes educator
Dia*Life*: Dia*Life*—Living Together with Diabetes
DM: Diabetes mellitus
VDBD: German Association of Diabetes Nurses and Education experts
